# Product quality control

Nordic Naturals will supply the fish oil supplement. This company follows the FDA guidelines for Good Manufacturing Procedures and verifies product quality and label claim by in-house and outside lab analysis. The fish oil capsules are tested for contaminants (e.g. heavy metals), lipid oxidation, and for omega-3 fatty acid content.

Analysis of outcome variables

The major outcome measures in this study are the 3-month change in MADRS and IFN-. Initially we will compare the difference in MADRS scores, BDI scores, and IFN- levels between the fish oil and placebo groups using a two-sample t-test. In a more exploratory analysis, we will then assess whether the change in IFN- levels is correlated with the change in MADRS. To do this we will build a multiple regression model, where the predictors are the baseline MADRS or BDI and IFN- levels and the change in IFN- levels. We will additionally assess whether there is an interaction between baseline IFN- and fish oil supplementation by extending the above regression to include the interactions terms with fish oil. In order to control for potential confounders (specifically age, gender, education level, disability, and fatigue), variable selection schemes (all possible regressions using maximum R2 and backwards elimination of variable) will be used to determine if any of these potential confounders predict the dependent variable. If so, these potential confounders will be included in the regression models as covariates.

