Our primary objective, Aim 1, is to determine the treatment effect on depression by using the MADRS and BDI. We will also monitor adverse events by subjects self-report of general health and laboratory tests (metabolic panel, including liver function tests and prothrombin time). We will monitor worsening of depression and suicidal ideation using both depression inventories, BDI and MADRS. Our secondary objective, Aim 2, is to determine the treatment effect on inflammatory cytokine levels, as fish oils may exert its clinical effect by decreasing peripheral levels of proinflammatory cytokines. We will measure cytokines released from mitogen stimulated peripheral blood mononuclear cells (PBMCs) by immuno-assay. Compliance will be monitored by pill count and red blood cell fatty acid analysis. Data collected from this pilot study will be used to aid us in the design of a larger, multi-center clinical trial that could more fully evaluate the effectiveness of this therapy.

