**A. SPECIFIC AIMS**

Aim 1) To determine if fish oil supplementation is an effective and safe adjunctive treatment for mild to moderate depression in people with MS

A. We hypothesize that 3 months of fish oil supplementation will improve depression scores on the Montgomery-Asberg depression rating scale (MADRS) or Beck Depression Inventory (BDI) more than the placebo treated group. Subjects in both the placebo and fish oil group that have responded to treatment (> 50% improvement on MADRS or BDI) will have the option to continue on treatment for an additional 3 months to evaluate longer-term effects.

B. We hypothesize that fish oil at the doses given is safe in MS subjects with mild to moderate depression taking MS disease-modifying drugs and anti-depressants. We will monitor the following: effects on blood clotting by prothrombin time (PT/INR); metabolic function including liver function by comprehensive metabolic panel; adverse events reporting (includes subject’s report of general health and screening for worsening of depression by BDI and MADRS).

Aim 2) To determine the effects of fish oil supplementation on pro-inflammatory agents related to depression and MS.

We hypothesize that one mechanism by which fish oil may exert its clinical effect is by decreasing peripheral levels of proinflammatory agents (cytokines). We expect to see a decrease in peripheral levels of inflammatory cytokines in subjects treated with fish oil.

We will measure the following cytokines release from mitogen stimulated peripheral blood mononuclear cells (PBMC) at 2 baseline time points and then at 1, 3, & 6 months of supplementation: tumor necrosis factor alpha (TNF-α), interferon gamma (IFN-γ), interleukin 2 (IL-2), interleukin-6 (IL-6), interleukin-4 (IL-4), and interleukin-10 (IL-10).

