#### Statistical Analysis Statistical power and sample size

The study that used 2g/day of E-EPA reported a 9.3-unit difference between baseline and 4-week differences in placebo and active groups for the HDRS, this difference was statistically significant (p < 0.001) [5]. The standard deviation for the groups was 7.4 (the larger of the standard deviations). A sample size of 11 subjects per group provides 80% power with an alpha= 0.05, to detect the above difference in HDRS between the treatment and placebo group. A sample size of 18 subjects per group will provide power greater than 95% with an alpha= 0.05, to detect a difference of 500 units for IFN- levels between baseline and post-treatment levels. This assumes a standard deviation of 400 units and is based on the results of a study that reported a decrease in IFN- levels in MS patients with MDD from baseline values after 16-wks of either therapy based or medication based treatments for depression [8]. Assuming a dropout rate of 20% the sample size of 60 subjects, or 30 per group is also more than adequate to detect a treatment difference in IFN- levels produced from PBMC. The additional sample will provide additional power for the exploratory analyses using the regression analysis. We are using the MADRS as the primary outcome measure as it is highly correlated with the HDRS [26-28] and will be more sensitive to treatment change in patients with MS than the HDRS. As we expect MADRS scores to have a greater change with treatment than the HDRS, we are well powered with 60 subjects.

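### The power section makes MADRS the primary outcome, but Aim 1's efficacy hypothesis accepts MADRS or BDI; either-scale success carries about 7-10% false-positive risk, not 5%

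*Protocol*

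**What the plan says.** Four places in the Protocol bear on what decides the trial.

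- **Statistical power and sample size:** "We are using the MADRS as the primary outcome measure as it is highly correlated with the HDRS". This is MADRS alone, and it is the only place that uses the term primary outcome.
- **Specific Aims, Aim 1, hypothesis A:** three months of fish oil "will improve depression scores on the Montgomery-Asberg depression rating scale (MADRS) or Beck Depression Inventory (BDI) more than the placebo treated group". Either scale is enough.
- **Structured Scientific Abstract:** "Our primary objective, Aim 1, is to determine the treatment effect on depression by using the MADRS and BDI". Both scales are named, with no rule for combining them.
- **Analysis of outcome variables:** "The major outcome measures in this study are the 3-month change in MADRS and" IFN-gamma. BDI is absent, and a cytokine stands beside MADRS. The abstract ranks cytokines lower: "Our secondary objective, Aim 2, is to determine the treatment effect on inflammatory cytokine levels".

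Analysis of outcome variables then compares MADRS, BDI and IFN-gamma between groups by two-sample t-test as the initial analysis. Only the later regression work is described as more exploratory. A level of 0.05 appears twice, both times in the power statements: once for the HDRS, which stands in for MADRS, and once for IFN-gamma. No level is given for BDI.

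**The concern.** The hypothesis under Aim 1 and the named primary outcome lead to different decision rules. Under the hypothesis, a significant difference on either depression scale confirms efficacy. Under the power section, only MADRS does. The two rules disagree when BDI is significant and MADRS is not: Aim 1 is then met while the primary outcome is missed, and the document does not say which statement governs.

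Such a split is plausible. BDI is self-reported and MADRS is clinician-rated, and the Assessments section treats their agreement as something still to be examined.

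An either-scale rule is also not a 5% test unless the level is divided. The trial is a pilot, but Aim 1 asks whether the supplement is effective, and the data are meant to shape a larger multi-center trial. A claim resting on whichever scale succeeded would tend to carry an overstated effect into that design.

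**Working it through.** **1. Inputs**

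| Input | Value | Source |
|---|---|---|
| Level | 0.05 | Power statements only (HDRS and IFN-gamma) |
| Difference, SD | 9.3 and 7.4 HDRS units | Statistical power and sample size |
| Sample size for 80% power | 11 per group | Same section |
| Enrolled, dropout | 30 per group, 20% | Same section |
| Correlation between MADRS and BDI results | Not given; assumed 0 to 0.9 | Assumption |

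**2. The plan's own figure.** Sidedness is not stated, so I checked which reading returns 80%. With 11 per group the noncentrality is 9.3 / (7.4 × √(2/11)) = 9.3 / 3.155 = 2.95 on 20 degrees of freedom. The noncentral t distribution gives 80.05% power two-sided and 88.5% one-sided. The stated 80% is reproduced by a two-sided test at 0.05, so I use that below.

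**3. MADRS alone (power section).** One test at 0.05: false-positive chance 5%.

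**4. MADRS or BDI (Aim 1, hypothesis A).** Under no effect on either scale, the chance that at least one test is significant is

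1 − P(|Z₁| ≤ 1.96 and |Z₂| ≤ 1.96),

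where Z₁ and Z₂ are the two test statistics, taken as bivariate normal with correlation ρ. For ρ = 0 this is 1 − 0.95² = 9.75%. For other values it was simulated with 4 million draws:

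| Assumed ρ | At least one of two tests significant |
|---|---|
| 0 (exact) | 9.75% |
| 0.3 | 9.5% |
| 0.5 | 9.1% |
| 0.7 | 8.3% |
| 0.8 | 7.8% |
| 0.9 | 7.0% |

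These count significance in either direction. Counting only results that favor fish oil roughly halves both sides of the comparison (2.5% for MADRS alone; 1 − 0.975² = 4.94% for either scale at ρ = 0), so the ratio is about the same.

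**5. Effect of the fix on power.** A single MADRS test at 0.05 is what the sample size already assumes. With 30 × 0.8 = 24 evaluable per group and the plan's own HDRS inputs, the noncentrality is 9.3 / (7.4 × √(2/24)) = 4.35, and power is 98.9%.

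**The case against.** The strongest reply is that the Protocol does name one primary outcome in advance. Read with the power section, a BDI-only result simply means that the primary outcome was not met. The abstract describes an objective, and an objective can be assessed with two instruments while one of them is primary. Analysis of outcome variables says major, not primary, and its pair can be read as the lead measure of each aim. Much of this stands. It weakens any suggestion that the sponsor is free to pick a scale afterwards, and it reduces the abstract and the analysis section to loose wording. It does not dispose of the hypothesis under Aim 1, which states an either-scale condition outright.

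A second reply is that test order and multiplicity are commonly left to a statistical analysis plan, which is not at hand. That is correct, so the point does not rest on a missing adjustment. It rests on statements in the Protocol that disagree, and an analysis plan could cite either of them.

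Two stronger readings are tempting, and the document does not support them.

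- A reader might count IFN-gamma as a third route to success and infer a false-positive risk of 12% to 14% (at most 1 − 0.95³ = 14.3% for three independent tests). No part of the Protocol lets an IFN-gamma result confirm efficacy against depression. Aim 2 is a separate, mechanistic and secondary aim. Independence would also sit poorly with the Background, which reports correlations of IFN-gamma measures with BDI of .54 and .64, although these are not correlations of change scores.
- A reader might infer that the plan tests each outcome at 0.05. The analysis section gives no level for any test, and BDI has none anywhere.

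**Conclusion.** The contradiction is real. The firm conflict is between the either-scale hypothesis of Aim 1 and the power section's MADRS-only primary outcome. The abstract and the analysis section add ambiguity, the latter by setting IFN-gamma beside MADRS.

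Under the hypothesis as worded, the false-positive chance is about 7% to 10%, against 5% under the power section. This rests on three assumptions: success is declared if either scale is significant; each scale is tested two-sided at 0.05, which for BDI is inferred because no other level is given; and the correlation between the scales, which the document does not give, lies between 0 and 0.9.

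This should be fixed, but it is not a bar to the trial. The study is a pilot, MADRS is already named in one place, and no design feature has to change.

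**What to change.** State once, and use throughout, that the single primary outcome is the 3-month (week 12) change in MADRS, tested two-sided at 0.05. Then align the other places:

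- **Specific Aims:** in the Aim 1, hypothesis A sentence, replace the either-scale condition with MADRS.
- **Abstract:** say that the primary objective is assessed by MADRS, with BDI as a secondary clinical outcome.
- **Analysis of outcome variables:** name MADRS as primary, BDI as secondary, and IFN-gamma as the lead outcome of Aim 2, which is secondary.

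The either-scale responder rule for entering the continuation phase is not a test of efficacy and is not part of this change.

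The cost is wording in three places, and that BDI alone can no longer confirm efficacy. Sample size, visits and assessments stay as they are. The change should be made before unblinding, because a choice of scale made later could not be shown to be independent of the results.

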#### Visit 1 (Screen)

The screening visit is to establish eligibility for study participation. This visit and all subsequent visits will take place at the MS Center of Oregon at OHSU or at the General Clinical Research Center (GCRC) at OHSU. Each potential study subject will be consented at this visit after which a family and medical history will be taken. The subject will be screened for major depressive disorder using the SCID, dementia by the MMSE, and for mild to moderate depression using the MADRS. They will then be asked to fill out the BDI. Concomitant medications will also be recorded at the screening visit (*See Table 1: Study Schedule: Phase I*).

Visit 2 (Baseline)

Subjects that meet study inclusion after the screening visit will be scheduled for follow up within 2 weeks. At this visit subjects will receive a brief physical exam and a neurological exam (EDSS) from [name]. The subject will be given a MADRS score. A research assistant will administer the MS Functional Composite (MSFC) and record concomitant medications. The subject will fill out study questionnaires which include: BDI, Multiple Sclerosis Quality of Life Inventory (MSQLI), and Food Frequency. A research assistant will draw blood for cytokine levels, prothrombin time (PT/INR), comprehensive metabolic panel, and RBC fatty acid analysis.

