#### Randomization

After study eligibility is established subjects will be randomized to placebo or fish oil supplementation by using a computer-generated scheme. Because of sample size limitations we will only stratify on one parameter prior to randomization, which will be the BDI score at screening. Subjects will be stratified into two categories “mildly depressed” with BDI scores 10-17 and “moderately depressed” with BDI scores 18-30. This will insure that each group will contain equal numbers of mild and moderately depressed subjects. The data management coordinator that is in charge of labeling medication will maintain the randomization list.

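### The fish oil versus placebo t-test adjusts for neither baseline nor the randomisation stratum: valid, but gives up precision that a change of wording would recover

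*Protocol*

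**What the plan says.** In section D, under Analysis of outcome variables, the protocol states: "The major outcome measures in this study are the 3-month change in MADRS" and in IFN-gamma. It then compares MADRS scores, BDI scores and IFN-gamma "levels between the fish oil and placebo groups using a two-sample t-test". No covariate or stratum is named. The power section adds: "We are using the MADRS as the primary outcome measure".

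The information needed for adjustment is collected. At Visit 2 (Baseline), "The subject will be given a MADRS score", and Table 1 schedules BDI and cytokines at the same visit. Under Randomization, "we will only stratify on one parameter prior to randomization, which will be the BDI score at screening", with strata 10-17 and 18-30.

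Baseline scores enter only a later model. It is introduced with "In a more exploratory analysis, we will then assess whether the change in" IFN-gamma goes with the change in MADRS, and continues: "we will build a multiple regression model, where the predictors are the baseline MADRS or BDI", together with baseline IFN-gamma and its change. Fish oil comes in through an extension with interaction terms. For age, gender, education, disability and fatigue, "variable selection schemes (all possible regressions using maximum R2 and backwards elimination of variable) will be used". The stratum is not on that list.

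**The concern.** The protocol itself names the test of the treatment effect, so this is a choice it makes and not a detail left open for a statistical analysis plan. Two baseline quantities that probably predict the week-12 score, the outcome's own baseline and the severity stratum, play no part in that test as model terms.

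The exploratory regression does not fill the gap. It asks a different question (cytokine change against mood change), conditions on a variable measured after randomisation, and chooses its other covariates from the data. No analysis in the protocol therefore estimates the fish oil effect adjusted for baseline.

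At stake is the width of the interval around the treatment difference in a pilot with about 24 evaluable subjects per arm, whose stated purpose is to inform a larger trial. Also at stake is how far a chance baseline difference between arms can move that estimate.

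**Working it through.** **Inputs from the protocol.** Difference 9.3 and SD 7.4 (HDRS), alpha 0.05, 11 per group for 80% power; 18 per group for more than 95% power on IFN-gamma (500 units, SD 400); 60 randomised, 20% dropout; MADRS entry range 11-30. Evaluable per arm: 30 × 0.8 = 24.

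**Assumed, because the protocol gives neither.** r, the correlation between baseline and week-12 MADRS, from 0.3 to 0.7; and k, the baseline SD divided by the follow-up SD.

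**1. The protocol's own figures.** An unadjusted two-sided t-test (noncentral t) with 9.3/7.4 has 80.05% power at 11 per group and 75.7% at 10, so 11 reproduces. For IFN-gamma, 18 per group gives 95.4%, which also reproduces. At 24 per arm, power for 9.3/7.4 is 98.9%.

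**2. Variance under each analysis.** In units of the follow-up variance:
- t-test on week-12 scores: 1
- t-test on change: k² + 1 − 2rk
- ANCOVA on baseline: 1 − r²

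The reduction from ANCOVA is therefore r² against week-12 scores, whatever k is, and (k − r)² / (k² + 1 − 2rk) against change. With k = 1 the latter becomes (1 − r)/2.

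**3. A narrower baseline.** Scores spread evenly over 11-30 would have SD 19/√12 = 5.5. If the follow-up SD were 7.4 (the HDRS figure, borrowed for illustration), k = 5.5/7.4 = 0.74. Then:
- r = 0.3: 0.44² / (0.5476 + 1 − 0.444) = 0.1936/1.1036 = 17.5%
- r = 0.5: 0.24² / (0.5476 + 1 − 0.74) = 0.0576/0.8076 = 7.1%
- r = 0.7: 0.04² / (0.5476 + 1 − 1.036) = 0.0016/0.5116 = 0.3%

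| Variance reduction from ANCOVA | r = 0.3 | r = 0.5 | r = 0.7 |
|---|---|---|---|
| against change, k = 1 | 35% | 25% | 15% |
| against change, k = 0.74 | 18% | 7% | 0.3% |
| against week-12 scores | 9% | 25% | 49% |

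For a t-test on change with k = 1, these gains equal 1/0.65 = 1.54, 1/0.75 = 1.33 and 1/0.85 = 1.18 times the sample. With k = 0.74 and r = 0.5 the factor is only 1/0.929 = 1.08.

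**4. In points, equal variances, 24 per arm.** Taking 7.4 as the SD of change, the t-test detects 6.11 points with 80% power. ANCOVA detects 6.11 × √0.65 = 4.93, 6.11 × √0.75 = 5.29 and 6.11 × √0.85 = 5.64 points. Power at 6.11 points rises from 80% to 93.5%, 89.9% and 86.0%. If 7.4 is instead the SD of week-12 scores and the t-test is on those, power rises to 83.6%, 89.9% and 97.5%. The one or two degrees of freedom spent on covariates are neglected.

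**5. Chance imbalance.** If the arms differ by d points at baseline, the expected difference in change shifts by (r/k − 1)d. At k = 1 and r = 0.5 that is half a point per point of imbalance. At k = 0.74 and r = 0.7 it is (0.946 − 1)d, about 0.05 point per point.

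**6. Validity and the stratum.** A simulation used 48 evaluable subjects, two equal strata, 6,000 runs per setting, an assumed correlation of 0.6 between BDI and MADRS, and equal variances. Type I error was 4.0-4.8% for the t-tests and 4.7-5.2% for ANCOVA with baseline and stratum. Power at an effect of 0.8 SD was:

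| r | t-test, week-12 | t-test, change | ANCOVA |
|---|---|---|---|
| 0.3 | 77% | 64% | 80% |
| 0.5 | 78% | 78% | 88% |
| 0.7 | 78% | 94% | 96% |

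**The case against.** The strongest reply is that a simple prespecified t-test is valid and adequate for a pilot. It has four parts.

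- **Baseline is already used.** A reader might infer that the test disregards baseline altogether. The documents do not support that: the outcome is defined as the 3-month change, and the power calculation also rests on a difference in changes. A t-test on change subtracts baseline. What stands is narrower: subtraction fixes the slope at 1 and does not estimate it. The wording of the comparison sentence also leaves week-12 scores possible.
- **Power is ample.** A reader might infer a trial short of power. On the protocol's own 9.3/7.4 it is not: power is about 99% with 24 per arm. That effect, however, comes from a 20-patient, 4-week study on another scale, and the Background itself reports that depression in MS is harder to treat than earlier work suggested. The gain counts if the effect is smaller, and for the interval estimate whatever the effect.
- **The gain may be small.** This stands. The entry range restricts baseline MADRS, and when k is close to r a t-test on change loses almost nothing.
- **The stratum matters little.** This largely stands. Leaving it out makes standard errors somewhat too large, but simulated type I error was still 4.0% or more. Its contribution beyond baseline MADRS was not isolated. Stratifying also gives some protection by design against severity imbalance.

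**Conclusion.** The point holds as one of efficiency. The planned comparison adjusts for neither the outcome's baseline nor the randomisation stratum, and nothing else in the protocol supplies an adjusted treatment effect. Apart from one or two degrees of freedom, ANCOVA is no less precise under either reading of the t-test.

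The size is uncertain. For r between 0.3 and 0.7 the variance reduction against change scores runs from 35% down to 15% with equal variances, and from 18% to practically zero with a baseline SD 0.74 of the follow-up SD. Against week-12 scores it is 9% to 49%. Neither r nor the variance ratio is in the protocol, and the SD of 7.4 belongs to the HDRS, not the MADRS. No figure can be given for IFN-gamma, since no baseline correlation or variance ratio is stated; there the case rests on the general argument alone.

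It would go too far to call the t-test biased or invalid, or to say that the trial cannot meet its stated power. The documents and the calculations support neither. This is a worthwhile correction that does not put the trial's conclusions at risk.

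**What to change.** Under Analysis of outcome variables, replace the t-test as the primary analysis with an ANCOVA of week-12 MADRS (or its change, which gives the same treatment estimate once baseline is in the model) on treatment, Visit 2 MADRS and the screening-BDI stratum. Fix these terms in advance and keep them out of any variable selection. Analyse BDI and IFN-gamma in the same way, each with its own baseline. Keep the two-sample t-test as a supportive analysis and say whether it is on change or on week-12 scores.

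A repeated-measures version that also uses the week 4 and week 8 MADRS already in Table 1 is optional.

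The cost is a change of wording and one or two degrees of freedom. No extra visits, data or subjects are needed, and the sample size can stay as it is.

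### The exploratory IFN-γ regressions omit treatment from the mechanism model, keep a post-randomisation variable in the moderation test, and use a covariate-selection rule that is not coherent

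*Protocol*

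**What the plan says.** All the relevant text is in Protocol section D, Analysis of outcome variables. The arms are first compared on MADRS, BDI and IFN-γ with two-sample t-tests. Three further steps follow.

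- **Mechanism model.** "In a more exploratory analysis, we will then assess whether the change in" IFN-γ goes with the change in MADRS. For this, "we will build a multiple regression model, where the predictors are the baseline MADRS or BDI and" IFN-γ at baseline, plus the change in IFN-γ. Treatment is not in the list.
- **Moderation model.** Whether baseline IFN-γ modifies the fish oil effect is tested by "extending the above regression to include the interactions terms with fish oil". IFN-γ change therefore stays in. The text does not say whether a fish oil main effect is added.
- **Covariates.** There are five candidates: "specifically age, gender, education level, disability, and fatigue". To choose among them, "variable selection schemes (all possible regressions using maximum R2 and backwards elimination of variable) will be used", judged by whether they predict the dependent variable. "If so, these potential confounders will be included in the regression models as covariates". No subset size, penalty or removal threshold is given, and nothing says which scheme decides if the two disagree.

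The sample size section adds that the subjects beyond the calculated minimum are there partly to give power to these regressions.

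**The concern.** Section A expects fish oil both to improve depression and to lower cytokines, and offers the second as one mechanism for the first. If both expectations hold, treated subjects tend to have larger falls in MADRS and in IFN-γ. A model that pools the arms without a treatment term then attributes part of the difference between arms to IFN-γ change, even if the two changes are unrelated within each arm.

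The moderation test has a different fault. IFN-γ change is measured after randomisation and is expected to respond to treatment. Holding it constant removes whatever part of the modification passes through it, which is the pathway the protocol proposes. It can also create an interaction if an unmeasured factor drives both changes.

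The covariate rule combines two procedures that need not agree. It also selects on prediction of the outcome alone, whereas confounding of the IFN-γ-change coefficient depends on a covariate's relation to IFN-γ change as well.

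At stake are the mechanism and effect-modifier conclusions that this pilot would carry into the larger trial described in section E(h).

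**Working it through.** **Inputs from the protocol.** Sixty subjects, 30 per arm, 20% dropout: 60 × 0.8 = 48 analysable. Depression: the cited trial "reported a 9.3-unit difference between baseline and 4-week differences" on the HDRS, SD 7.4, so 9.3/7.4 = 1.26 SD. IFN-γ: 500 units, SD 400, so 500/400 = 1.25 SD.

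**The protocol's own figures.** With two-sided alpha 0.05, 11 per group gives 80.05% power for 9.3 with SD 7.4 (two-sample t), as stated. For 500 with SD 400, 18 per group gives 95.4% (two-sample t), consistent with the stated figure of more than 95%. The protocol states no error rate for the regressions, so these were simulated by least squares at nominal 5%, with 4,000 replicates per scenario (standard error about 0.3 percentage points near 5%).

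**1. Omitted treatment.** Take equal arms, unit within-arm SDs, no within-arm link, baselines unrelated to the changes, and treatment effects d1 on MADRS change and d2 on IFN-γ change. The treatment indicator has variance 1/4, so the pooled covariance is d1·d2/4, the pooled variance of IFN-γ change is 1 + d2²/4, and the spurious slope is (d1·d2/4)/(1 + d2²/4).

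| d1, d2 (SD) | Slope by formula | False link, planned model, N=48 | With treatment term |
|---|---|---|---|
| 0, 0 | 0 | 5.7% | 5.6% |
| 0.25, 0.25 | 0.0156/1.0156 = 0.015 | 5.7% | 5.7% |
| 0.5, 0.5 | 0.0625/1.0625 = 0.059 | 6.9% | 4.8% |
| 0.8, 0.8 | 0.16/1.16 = 0.138 | 14.9% | 5.1% |
| 1.257, 1.25 | 0.393/1.391 = 0.282 | 49.5% | 5.3% |

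The simulated slopes in the last three rows (0.059, 0.139, 0.285) agree with the formula. A separate simulation gave 7%, 14% and 50% for the same three rows. If only one outcome is affected, the rate stays near 5%. With all 60 subjects analysed, the last row becomes 60.6% against 5.2%.

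**2. Moderation.** Assumed scenario, with T for treatment and B for standardised baseline IFN-γ: IFN-γ change = −1.25T − 0.8·T·B + error; MADRS change = 0.8 × IFN-γ change + error. The true T×B effect on MADRS change is 0.8 × (−0.8) = −0.64. Given IFN-γ change it is 0. Simulated at N=48, with the fish oil main effect included (the favourable reading):

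- without IFN-γ change: −0.64, detected in 35.8% of trials;
- with IFN-γ change: about 0, detected in 5.3%.

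In the opposite case IFN-γ has no effect on MADRS, but an unmeasured factor loads on both changes with weight u, and the fish oil effect on IFN-γ changes by θ per SD of B. Conditioning on IFN-γ change creates an interaction of θ·u²/(u²+1). With θ = 0.8 this is 0.31 at u = 0.8 and 0.40 at u = 1.0, with false-positive rates of 13.3% and 16.8%. With θ = 0.5 and u = 0.8 the rate is 7.9%. Without IFN-γ change in the model it is 4.9 to 5.7%.

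**3. Selection.** R² cannot fall when a variable is added, so its maximum over all 32 subsets of five covariates is always the full set. Backward elimination can stop elsewhere. With five unrelated covariates, the chance of keeping at least one is approximately 1 − 0.95⁵ = 22.6% at p<0.05 or 1 − 0.90⁵ = 41.0% at p<0.10. False-positive rates at N=48 (covariate effects and thresholds assumed; ranges cover removal at 0.05 and 0.10):

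| Effect of each covariate on both changes | IFN-γ change: backward elimination | All five fixed | No covariates |
|---|---|---|---|
| 0 | 5.5% | 4.7–4.8% | 4.6–5.1% |
| 0.2 SD | 11.6–14.0% | 4.6–5.3% | 19.6–20.2% |
| 0.3 SD | 19.1–27.5% | 4.9–5.1% | 56.0–56.7% |

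For a treatment term under the same schemes, backward elimination gives 5.4 to 7.7% and fixed covariates 4.7 to 5.5%.

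**The case against.** The case for leaving this alone has real weight.

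- **The analyses are labelled exploratory, in a pilot.** This is correct and limits the importance of the point. It does not repair a model that cannot separate a mechanism from two parallel effects.
- **The stated question is correlation, not mediation.** Across pooled arms the two changes would indeed be correlated, so the error lies in reading that as a mechanism. But section A poses the question as a mechanism, and the result would be read that way.
- **The extended model probably contains a fish oil main effect.** This is the usual reading, but it is not stated, and the first model still lacks one.
- **The 50% figure uses effects that are not this trial's.** This stands. The 500 units are a change from baseline under psychotherapy or medication for depression, not a fish oil versus placebo difference, and 9.3 is on the HDRS rather than the MADRS. At 0.5 SD or less the excess is small.
- **The lost interaction follows by construction.** It does, once the modification is assumed to run wholly through IFN-γ change. That is the case the protocol's own hypothesis makes relevant. Even without IFN-γ change, power is only about 36% in the assumed scenario.
- **Selection is the weakest part.** If maximum R² governs, all five covariates are adjusted for and the error rate is sound. Backward elimination also beats no adjustment. What remains is that the text does not say which procedure decides.

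A reader might infer that Aim 2, or the efficacy result, rests on these models. It does not: the aim of showing lower cytokines is tested, for IFN-γ, by a two-sample t-test between randomised arms.

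**Conclusion.** The point holds as a defect in how the exploratory mechanism and moderation models are specified. It does not touch the randomised t-tests on MADRS, BDI and IFN-γ, including Aim 2's direct comparison for IFN-γ.

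The omission of treatment matters only if fish oil affects both outcomes appreciably. Across the assumed effects the false-link rate runs from nominal (0.25 SD or less) to about one trial in two (about 1.25 SD). Keeping IFN-γ change in the moderation test mainly hides real modification. False modification needs a shared cause, for which the documents give no figure. The selection rule is incoherent as written; how far it inflates error depends on assumed covariate effects and thresholds, and the inflation is small for a treatment term.

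It would be tempting to conclude that these analyses will produce false findings. The documents support only that they can, under conditions the protocol itself hopes to see.

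**What to change.** Change the wording of Analysis of outcome variables in three places.

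1. **Mechanism model:** add treatment to the predictors, and report the IFN-γ-change coefficient as a within-arm association. It remains observational, because factors driving both changes within an arm are not removed.
2. **Moderation model:** regress MADRS change on baseline MADRS, treatment, baseline IFN-γ and treatment by baseline IFN-γ, without IFN-γ change.
3. **Covariates:** delete both selection schemes and name the five listed variables, at their baseline values, as fixed covariates.

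Fixing only one or two covariates would not reliably improve on the present text. With two of the five acting as confounders (assumed effects 0.35 SD on MADRS change and 0.4 on IFN-γ change, removal at p>0.10, N=48), the false-positive rate is about 12% with backward elimination, 12 to 13% if one true confounder is fixed, 29% if two irrelevant ones are fixed, and about 5% if all five are fixed.

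The cost is degrees of freedom. Counting one parameter per covariate, the mechanism model has intercept, two baselines, IFN-γ change, treatment and five covariates, so 48 − 10 = 38 remain, against 48 − 4 = 44 for the listed predictors alone. No visits, samples or subjects are added.
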